**Figure 1 figure1:**
[figure not shown]
WATCH study design. AF: atrial fibrillation; BC: breast cancer; ECG: electrocardiogram; RT: radiotherapy; SL-ECG: single-lead electrocardiogram; WATCH: Watch Your Heart After Radiotherapy for Breast Cancer.

The study was registered with ClinicalTrials (NCT06073509) on September 10, 2023.

### Ethics Approval

This study will be conducted in accordance with the Declaration of Helsinki (amended at the 64th World Medical Association General Assembly, Fortaleza, Brazil, October 2013) and the principles of Good Clinical Practice and the Medical Research Involving Human Subjects Act (WMO). This project aims to evaluate a medical device or a device used for nonmedical purposes and is framed by Regulation (EU) 2017/745 on medical devices (MDR). This study received ethical approval from the French Southwest Committee for Protection of Persons and from the National Agency for Medical and Health Products Safety (IDRCB number 2023-A01622-43). Participants enrolled in the study will provide written informed consent. To ensure privacy and confidentiality, all data collected in this study are de-identified prior to analysis, with no personally identifiable information retained.

### Study Population

In this study, we plan to include 200 female patients with unilateral BC, aged over 65 years old at inclusion and treated at least 5 years ago with postoperative modern photon-based RT after surgery. For this study, we will focus on patients aged >65 years, as recommended by the European Heart Rhythm Association [43], which concluded that systematic screening using intermittent ECG may be beneficial to detect AF in individuals aged >65 years with comorbidities increasing the risk of stroke. Patients with a history of cancer or AF before RT or with recurrent cancer (BC or other) after RT will be excluded. Inclusion and exclusion criteria are summarized in Textbox 1.

Inclusion and exclusion criteria.
**Inclusion criteria:**
Women surgically treated for left or right breast cancer (BC) and for whom adjuvant treatment is radiotherapy (RT), with irradiation of the breast or chest wall irradiation and possibly ganglion chainsAdjuvant RT performed between 5 years before enrollmentA 5-year post-RT follow-up oncologist consultation performed in one of the investigating centersAge 65 years or more at enrollmentOwning a smartphone and able to understand and use digital tools alone or with the help of a caregiverConsented to a connected follow-upAffiliated with a social security system or equivalentVolunteering to participate in the study and providing signed informed consent
**Exclusion criteria:**
History of cancer before RT for BCHistory of atrial fibrillation (AF) before RT for BCRecurrent cancer (BC or other) after RT for BC

### Recruitment and Study Procedures

Patients will be enrolled at the Clinique Pasteur in Toulouse and at the François Baclesse Center for Cancer Control/Caen University Hospital in Normandy. Until now, enrollment has begun only at the Clinique Pasteur.

#### Before Inclusion

Potential participants undergo prescreening by the oncologist during their final post-RT follow-up consultation (approximately 5 years after RT) to ensure eligibility. This is performed before any study procedure is conducted. The participants are enrolled formally only after they sign the informed consent form at the inclusion visit.

#### Inclusion Visit

Participants complete a medical questionnaire to provide information about their medical history prior to RT and all treatments and cardiovascular diseases that may have occurred since the end of RT (see details in the *Data Collection* section). The participants then receive the *Withings ScanWatch* (Withings SA) smartwatch, and they install the Withings HeathMate app on their smartphone to continuously record their cardiac activity and register ECGs. The watches are purchased by the Authority for Nuclear Safety and Radiation Protection (ASNR), the study sponsor. The choice of Withings ScanWatch was based on several reasons. Many smartwatches integrated with ECG recording currently meet the European Conformity (CE) standards. A recently published study [31] concluded that all evaluated devices have high diagnostic accuracy. An inclusion criterion for the WATCH Study specifies that patients must own a smartphone, with no restrictions on the smartphone brand. An analysis of the user manuals of the different watches led us to choose Withings ScanWatch, as it is the only one compatible with all smartphone brands. Moreover, feedback from the cardiologists involved in the study was positive regarding this smartwatch: accurate ECG recordings, quite simple for patients to use, and good battery life. It should be noted that there was no conflict of interest among the investigators in the choice of Withings ScanWatch.

The functions of the smartwatch and its application are explained to the participants. They are required to wear the loaned smartwatch for 1 month and record an ECG at least once per day or when the smartwatch automatically detects an abnormal heart rhythm and suggests that the user record an ECG.

#### Screening Visit

One month after the inclusion visit, all recorded smartwatch-based ECG data are emailed as a PDF file by the patients to the study cardiologists. To prevent data collection failure due to elderly adults’ unfamiliarity with smartphone usage, especially when sending an email with a PDF file attached, practice time is scheduled during the screening visit with clinical researchers (practice for 1 hour). During this visit, if necessary, patients can be accompanied by their caregivers, who will be able to transfer the PDF files. The patients complete a questionnaire to evaluate their satisfaction with and the usability of the smartwatch integrated with ECG recording, reset the smartwatch, and return it. The smartwatch is then loaned to another patient enrolled in the study. Finally, a cardiology consultation including a 12-lead ECG completed with transthoracic echocardiography (TTE), providing a comprehensive assessment of cardiac structures and functions, is performed (see details in the *Data Collection* section). Criteria for diagnosing asymptomatic AF and AF using instruments and auxiliary examinations in this study will follow the most recent guidelines for AF management [57].

### Data Collection

#### Cancer, Treatment, and Medical History Before and After RT

Information about cancer and its treatment (surgery, chemotherapy, RT, hormonotherapy) are collected through hospital medical records. The retrospective collection of information, which aims to identify cardiovascular diseases prior to RT and those that occurred between RT and 5 years post-RT, is based on medical questionnaires filled by the patients and checked against their medical records (see Textbox S1 in Multimedia Appendix 1).

#### Cardiac Examinations

The cross-sectional data collection, which aims to identify AF and other cardiac diseases at 5 years post-RT, not previously identified in the retrospective data collection, is based on screening for cardiac diseases. This screening is conducted by recording data from the Withings ScanWatch smartwatch, confirmed by an ECG, and validated by a cardiologist. In addition to AF screening, a 12-lead ECG and a TTE are performed (see Textbox S2 in Multimedia Appendix 1). Patient satisfaction with and usability of the smartwatch are assessed using a satisfaction survey [58] and the System Usability Scale (SUS) score [59] (see Textbox S3 in Multimedia Appendix 1).

#### Cardiac Dosimetry

For cardiac dosimetry, autosegmentation algorithms are being developed based on AI/deep learning to assess the radiation dose to potentially critical substructures for the occurrence of AF (whole heart, cardiac chambers, sinoatrial node, atrioventricular node, coronary arteries, PVs). These algorithms will use convolutional neural networks trained on large datasets of annotated computed tomography (CT) images to identify and contour cardiac substructures with high precision. Specifically, the model used in this study will be trained and validated using a dataset of CT images annotated by expert radiation oncologists and cardiologists to ensure anatomical accuracy and reproducibility [47,50]. Validation metrics, such as the Dice similarity coefficient (DSC), the Hausdorff distance, and the mean surface distance, will be used to evaluate the model’s performance against expert contours.

For each patient included in the WATCH cohort, CT images are collected with Digital Imaging and Communications in Medicine (DICOM) data. These CT images will be contoured with our deep learning segmentation tool to provide mean radiation doses and dose-volume histograms for all critical cardiac substructures. The application of AI in this study will allow for reproducible, time-efficient, and standardized dosimetry, addressing interobserver variability associated with manual contouring. Furthermore, the algorithms will be tested for robustness across different scanner models and imaging protocols to ensure generalizability. Nevertheless, manual review and correction by experienced clinicians will be performed for a subset of cases to further verify segmentation accuracy and consistency, aligning with the best practices for incorporating AI in clinical research.

### Outcome Measurement

#### Primary Outcome

The difference in the occurrence of AF (questionnaire + SL-ECG based) throughout the 5-year follow-up after RT according to heart exposure (moderate or low exposure: <75th percentile of radiation dose distribution for the whole heart; and high exposure: ≥75th percentile of radiation dose distribution) will be measured as the primary outcome of interest for this study.

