**Results:**

Enrollment started in October 2023 and will continue until mid-2026 to include 200 patients, which will ensure an 80% statistical power to detect a significant difference in AF incidence around 15% for the group of patients moderately exposed (<75th percentile of the mean heart radiation dose) and 25% for the group of patients highly exposed (>75th percentile of the mean heart radiation dose). The results are expected by the end of 2026.

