**Conclusions:**

This study will contribute to generating new knowledge on AF after RT for BC and help considering the inclusion of AF screening into routine clinical practice for these patients. Identifying the dose-risk associations would improve RT delivery protocols to limit the occurrence of different forms of AF and, if necessary, initiate appropriate treatment.

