### Study Rationale

Studies on AF and its potential link with RT for BC are relatively limited and have several limitations: the probable undercapture of AF events, particularly in the case of silent AF; the lack of details on the identification or diagnosis of AF; and the lack of precise dose metrics data for cardiac substructures.

In the population of patients with BC treated with RT, asymptomatic forms of AF are often missed in retrospective data collection, which typically identifies only symptomatic cases. Our study hypothesizes that at the time of the last follow-up visit (ie, 5 years post–breast RT by an oncologist), an opportunistic single-timepoint screening combining the use of a smartwatch and a cardiological evaluation, including an ECG and an echocardiogram, could help identify these asymptomatic cases. This would facilitate the management and potential treatment of these patients and increase the completeness of identifying incident cases potentially associated with RT.

Cardiac irradiation related to RT for BC can lead to an increased risk of cardiovascular diseases a few months to several years after treatment. However, precise data for AF, to establish a potential dose-response relationship, are sparse. Our study hypothesizes that the risk of AF could be associated with the radiation dose absorbed by critical cardiac substructures.

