### Sample Size Calculation

The calculation of the required sample size was conducted within the framework of an exploratory study. The required number of patients was set to 200 based on a statistical power of 80% with a type I error rate of 5% and theoretical percentages of AF incidence of 10% for the group of patients considered moderately exposed (<75th percentile of the average heart radiation dose distribution) and 25% for the group of patients considered highly exposed (>75th percentile of the average heart radiation dose distribution) [60]. We plan to include these 200 patients in approximately 30 months.

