### Planned Statistical Analysis

We will summarize the baseline data (description of the cancer and treatments, history of cardiovascular diseases, cardiac dosimetry) using descriptive statistics: means (SDs) will be used for continuous data with a normal distribution, medians (IQRs) for skewed data, and percentages for categorical data. Continuous data will be compared between cases and noncases of AF using the *t* test or the Wilcoxon Mann-Whitney test, and categorical variables will be compared using the chi-square test. All tests will be bilateral, with α=5%.

The estimation of the incidence of AF and other cardiovascular pathologies occurring in the 5 years following RT will be carried out based on data collected during the cardiology consultation (SL-ECG screening, 12-lead ECG, and echocardiography) and the medical questionnaire. A univariate analysis using regression models will identify the risk factors associated with the studied cardiovascular pathologies, other than cardiac radiation exposure (ie, individual and medical characteristics). Subsequently, only variables with *P*<.20 will be retained for multivariable analyses [61]. Estimations of the risk of AF and other cardiovascular diseases according to cardiac radiation doses will be performed using regression models adjusted for the risk factors identified in the univariate analysis. To limit issues in the multivariate analysis due to correlation between dosimetry parameters, each dosimetry parameter will be analyzed separately. Analysis will be performed using the data analysis and statistical software SAS version 9.4.

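### The primary comparison cuts a continuous heart dose at its 75th percentile, with no value in Gy; if the log-odds of AF rise about linearly with dose, this costs about 13–17 points of power

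*Protocol article*

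**What the plan says.** The Primary Outcome section defines two groups by whole-heart dose: "moderate or low exposure: <75th percentile of radiation dose distribution for the whole heart; and high exposure: ≥75th percentile of radiation dose distribution". The Sample Size Calculation uses the same division. It assumes an AF incidence of "10% for the group of patients considered moderately exposed" and "25% for the group of patients considered highly exposed (>75th percentile of the average heart radiation dose distribution"), with 200 patients, 80% power and a 5% type I error. The abstract's Results paragraph gives a different lower rate: "AF incidence around 15% for the group of patients moderately exposed". The Planned Statistical Analysis section makes all tests two-sided at 5%.

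No section gives the cut in Gy or names an outside reference distribution, so the natural reading is the 75th percentile of the enrolled cohort.

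The Cardiac Dosimetry section provides mean doses and dose-volume histograms from each patient's planning CT, so dose will be available as a continuous measure. On purpose, the abstract's Conclusions say "Identifying the dose-risk associations would improve RT delivery protocols". The Study Rationale says that "precise data for AF, to establish a potential dose-response relationship, are sparse", and the Discussion's Summary expects the regressions to clarify the dose-response association.

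**The concern.** A two-group contrast gives one number, the difference in AF between the top quarter and the rest. A patient just under the cut counts the same as one whose heart received almost nothing. The contrast therefore cannot show whether risk rises with dose.

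The boundary also depends on who is enrolled: the balance of left- and right-sided disease, the fields treated, and the contribution of a second centre that had not begun enrolment when the article was written. A high-versus-low estimate from this cohort does not convert to a risk per Gy, so it is hard to carry to another cohort or into treatment planning.

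The evidence in the protocol's Introduction is largely graded. It includes a dose-response relationship for mean heart dose in lung cancer, a similar association in breast cancer, and a 30% increase in AF risk per 10 Gy to the left atrium in oesophageal cancer. None of it points to a step at a cohort's 75th percentile. If the true relation is graded, the split also uses the data inefficiently.

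**Working it through.** **Inputs.** From the protocol: 200 patients; a split at the 75th percentile, hence about 150 and 50; two-sided α = 5%; AF 10% vs 25% (Sample Size Calculation) or 15% vs 25% (abstract). Assumed, because the protocol gives neither: the shape of the dose distribution and the shape of the dose-risk curve.

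**Step 1: the plan's own figure.** With the pooled normal approximation, power = Φ{[|p₂ − p₁| − 1.96 √(p̄(1 − p̄)(1/n₁ + 1/n₂))] / √(p₁(1 − p₁)/n₁ + p₂(1 − p₂)/n₂)}.

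- 10% vs 25%: p̄ = (15 + 12.5)/200 = 0.1375. The null SE is √(0.1375 × 0.8625 × 0.02667) = 0.0562 and the alternative SE is √(0.0006 + 0.00375) = 0.0660. Power = Φ[(0.15 − 0.1102)/0.0660] = Φ(0.603) = 72.7%.
- 15% vs 25%: p̄ = (22.5 + 12.5)/200 = 0.175. The SEs are 0.0620 and 0.0678. Power = Φ[(0.10 − 0.1216)/0.0678] = Φ(−0.319) = 37.5%.

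The stated 200 for 80% power is reproduced with two equal groups of 100 (two-sided, 10% vs 25%), not with 150/50. That is a separate sample-size error. The comparison below starts from the split's actual power, not from 80%.

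**Step 2: split against continuous dose, log-odds linear in dose.** For each assumed dose shape, logit P(AF) = a + b × dose was calibrated so that mean risk is 10% (or 15%) below the 75th percentile and 25% above it. In 4,000 simulated cohorts of 200 (Monte Carlo SE about 0.7 point), a chi-square test at the sample 75th percentile was compared with the logistic likelihood-ratio test on dose.

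| Assumed dose shape | 10% vs 25%: split | continuous | 15% vs 25%: split | continuous |
|---|---|---|---|---|
| Normal | 72.2% | 88.8% | 35.8% | 53.3% |
| Uniform | 72.9% | 88.7% | 36.4% | 51.4% |
| Log-normal, σ 0.4 | 73.1% | 86.6% | 37.4% | 50.6% |
| Log-normal, σ 0.6 | 72.8% | 88.9% | 37.8% | 54.6% |
| Log-normal, σ 0.8 | 73.5% | 90.4% | 37.0% | 56.7% |
| Gamma, shape 2 | 72.6% | 86.9% | 36.6% | 49.3% |
| Left/right mixture | 72.0% | 85.4% | 37.2% | 49.8% |

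The gap is 13–17 points at 10% vs 25% and 13–20 points at 15% vs 25%. A repeat simulation gave 72–74% against 87–89%, and 34–38% against 50–55%. If ranks replace dose in Gy, the gain at 10% vs 25% falls to 3–16 points.

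**Step 3: other curve shapes.**

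- Step at the cut (10% below, 25% above): the split has 68% and continuous dose 48–51%, so the split gains 17–20 points. Across all runs of this scenario its advantage was roughly 13–22 points.
- Monotone with a plateau (flat to the median dose, then rising, then level; AF about 8% to 28%), split against continuous: 71% vs 67% (normal), 77% vs 69% and 76% vs 64% (two log-normals), 71% vs 71% (left/right mixture). The gain disappears or turns into a loss.

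**Step 4: can a non-linearity check protect the continuous model?** Expected events at 10% vs 25% are 150 × 0.10 + 50 × 0.25 = 27.5. With a true step at the cut, a 3-knot restricted cubic spline test detected non-linearity in only about 5–13% of simulated cohorts.

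**Step 5: sampling error of the cut.** At n = 200 the sampling error of the 75th percentile is about 0.1 SD of dose for a normal shape. The missing Gy value is therefore a matter of interpretation and transfer, not of precision.

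**The case against.** The strongest reply is that the benefit of continuous dose rests on a curve the protocol does not supply. This stands. Monotonicity alone is not enough, as the plateau runs show, and a step at the cut favours the split clearly. Nor does the non-linearity check remove the risk of a wrong shape with so few events.

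Second, the split is not the only dose analysis. The Planned Statistical Analysis section plans adjusted regressions of AF on cardiac doses, one dosimetry parameter at a time, without saying whether dose enters as continuous or grouped. A reader might infer that the study throws its continuous dose data away. The protocol does not support that; the criticism reaches only the primary contrast.

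Third, the primary objective is AF incidence and its radiation and non-radiation risk factors. The association with absorbed dose is listed as a secondary objective, and the Limitations section says the exploratory study will compare high- and low-exposure groups. This is fair, but the primary outcome is itself a dose contrast, and the Discussion promises a dose-response association.

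Fourth, a percentile fixed in advance is not chosen by looking at outcomes. A reader might infer that the cut inflates the type I error. It does not. Reporting the observed cut-off in Gy answers much of the complaint about its meaning.

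**Conclusion.** The concern holds in conditional form. The primary contrast reduces a continuous dose to two groups at what is, on the natural reading, the cohort's own 75th percentile, with no value in Gy. That serves the stated dose-response and radiotherapy-delivery aims poorly.

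The cost is about 13–17 points of power at 10% vs 25% (13–20 at 15% vs 25%) if the log-odds of AF rise about linearly with dose. A flat statement that the split loses this power would go beyond the documents, which give no dose distribution and no curve: the difference can vanish or reverse. The graded evidence in the Introduction makes the continuous form a reasonable default but does not prove linearity.

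The shortfall from the stated 80% power has a different cause, unequal group sizes, and is not part of this point. The split remains a valid test, so this is a change that should be made, not a fatal flaw.

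**What to change.** Before the analysis begins (planned for June 2026), and without reference to outcome data:

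- Make the primary dose-risk test a logistic regression of AF on continuous mean heart dose, reported as an odds ratio per Gy, two-sided at 5%.
- Pre-specify one named non-linearity check, for example a restricted cubic spline with three knots, and state that with about 27 expected events it has little power, so a non-significant result does not establish linearity.
- Keep the 75th-percentile comparison as a supporting result and report its observed cut-off in Gy.

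The cost is an assumption about the shape of the dose effect and a documented amendment of the primary contrast after enrolment has begun, including the registry entry if it lists the split. No new data are needed.

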#### Secondary Outcomes

As mentioned before, the secondary outcomes are:

Cardiac substructure dosimetry (cardiac chambers, conduction nodes, coronary arteries, and PVs)Association between AF occurrence and cardiac substructure dosimetryOccurrence of other arrythmias and conduction disorders (12-lead ECG based) throughout the 5-year follow-up after RTOccurrence of other cardiac dysfunction, cardiomyopathies, and valvular heart diseases (TTE based) throughout the 5-year follow-up after RTAssociation between other arrythmias and conduction disorders or other cardiac diseases, and cardiac substructure dosimetryPatient satisfaction score using the Lickert scale and usability score using the SUS

